## Discussion

The primary focus of this study is to evaluate the smoking preventive intervention – X:IT II. We expect the revised version of the X:IT intervention to be equally successful in preventing smoking uptake in adolescents from high and low socioeconomic backgrounds. Smoking prevalence is higher among low SEP adolescents [1] and contributes to a large extent to the social inequality in health over the lifetime [5].

Public health interventions are often accused of leading to higher social inequality when implemented across populations [4]. School-based interventions to prevent smoking can also widen this inequality, however studies have also been found to reduce the gap; secondary analyses of three overall effective school-based European smoking interventions showed mixed results. One seemed to widen socioeconomic inequality, while the two other studies showed mixed results depending on which measure of socioeconomic status that were used [42]. One of the conclusions from the study was that adolescent smoking is also influenced by factors outside the school, especially smoking by parents and other significant relations, which are important to include when aiming at reducing the social inequality in intervention effects [42]. The changes conducted in the X:IT II intervention are based on thorough interview work with the target population of children from low social class and their parents. The changes should therefore be highly relevant and target some of the specific problems related to a smoking preventive intervention, such as the X:IT intervention.

The X:IT II intervention is based on an intervention which has been thoroughly evaluated and has proven effective, especially when implemented correctly. The X:IT II intervention target adolescent smoking from multiple levels simultaneously; the individual level, the family level, and the school level. This is recommended by the literature and must be considered state of the art in school-based smoking interventions [11]. The X:IT intervention is developed and adjusted by the Danish Cancer Society and will be evaluated by the Centre for Intervention Research. Especially in an intervention which is not a randomized controlled trial it is of great value, that the evaluating organization is independent from the organization that developed and implemented the intervention.

One of the limitations of this study is that we did not succeed in recruiting the required number of schools for a randomized design. The clustering of smoking in schools and classes leads to the need of a very high number of schools for an RCT, in this case 78 schools for intervention and 78 for comparison. The main purpose of the X:IT II study is to examine the differences between high and low SEP and the mechanisms behind these differences. The difference-in-difference design suits this purpose. There are two main assumptions to the difference-in-difference design, the assumption of parallel trends and the assumption of common shocks. First, the parallel trends assumption states that trends in outcomes between the exposed and comparison groups are parallel prior to the intervention. As we know from the literature, that smoking is more prevalent among both adolescents and adults from lower SEP [1, 43], it is not possible to fulfill this assumption. On the other hand, at the beginning of grade 7, very few students have become smokers and as such a trend in smoking is not calculable in this age group. We expect that the second assumption of common shocks stating that any events occurring during or after the intervention will equally affect the exposure and comparison groups, will be fulfilled. Power calculations for the difference-in-difference design showed a need for 48 schools, which was fulfilled in the recruitment where 57 schools gave consent to participate. However, as previously described only 46 schools participated in the baseline data collection.

To further improve the evidence from this study, a thorough process evaluation is planned including both qualitative and quantitative methods. The qualitative evaluation will seek to understand how teachers work with the intervention and under which circumstances the best implementation is obtained. Further, we will obtain knowledge and understanding on how students perceive and receive the intervention. The quantitative process evaluation will, as was the case in the former evaluation of X:IT, be based on students receiving the intervention. Also, school capacity to implement, as well as the actual obtained implementation, will be assessed. Like in the X:IT study [20, 25], we will conduct analyses taking the actual implementation into account in the effect evaluation. Hereby, we will be able to draw conclusions about the effectiveness of the X:IT evaluation. We will examine intervention effects in relation to the actual implementation at the school as well as the individual level. Numbers of students receiving the intervention in X:IT II is almost equal to the group of intervention pupils from the first evaluation. Analyses will therefore be comparable to each other.

If shown to be effective, the X:IT II study will provide important information on how to prevent smoking uptake effectively also among the group of adolescents from low socioeconomic backgrounds who are currently at higher risk of smoking uptake in Denmark.

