Schools are regarded suitable settings for prevention activities for children and adolescents, as the school setting offers the possibility to reach almost all within the relevant age group and across different socioeconomic positions [9, 10]. In the past decades, a large number of school-based smoking prevention programs have been implemented internationally, but evaluations have shown contrasting results regarding their effectiveness [11]. Generally, strategies using comprehensive components, including environmental strategies, have been found more effective than exclusively information based interventions, which have shown limited or no effect [12, 13]. The history of school based smoking prevention in Denmark includes participation in the international intervention study “The European Smoking Prevention Framework Approach” (ESFA). Unfortunately, there was no effect of ESFA in Denmark [14]. Two other school-based interventions in Denmark, “Smoke-free classes” and “Tackling” also reported no effect [15, 16].

In 2010, the Danish Cancer Society launched the X:IT intervention. The effect of the intervention was tested in a randomized controlled trial, testing the implementation in 53 Danish schools compared to 41 control schools from 2010 to 2013 [17]. X:IT turned out to reduce smoking uptake with up to 25% among participants after the first year of study [18]. However, the qualitative process evaluation showed that some of the intervention components were less appealing to children from lower socioeconomic positions [19], indicating that X:IT in the first version might have limited appeal to the group of adolescents from lower SEP. Therefore, the intervention components have been modified and an evaluation of this revised intervention X:IT II is needed to show whether pupils from different social backgrounds benefits equally from the intervention. This paper presents the modified X:IT II intervention and its intervention components as well as the design of the effect and process evaluation of X:IT II.

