### The X:IT trial

The first X:IT study was a large-scale cluster randomized controlled trial conducted in 94 schools testing the effectiveness of the X:IT intervention among 13- to 15-year-olds [17].

The intervention was developed and implemented by the Danish Cancer Society. The Centre for Intervention Research was responsible for thorough scientific evaluation of implementation and effect of the intervention [18–21]. The X:IT intervention was developed using the Intervention Mapping Protocol as a systematic planning tool [22] and the Theory of Triadic Influences as theoretical framework [23].

The X:IT intervention targeted all students attending grade 7 to 9 (13- to 15-year-olds) in the intervention schools and X:IT included three main intervention components:smoke free school groundsparental involvement comprising two dimensions – (a) smoke free contract between the student and an adult person, preferably a parent, (b) smoke free dialogues between student and parents/adultsa smoke free curriculum based on self-efficacy training and appraisal of outcome expectancies

The intervention was implemented from autumn 2010 until spring 2013 [17]. The effect evaluation showed the intervention to be effective in achieving its pre-specified aim of reducing smoking by 25% after the first year of intervention; the odds ratio for smoking among students attending an intervention school compared to control schools was 0.61 (95% CI: 0.45–0.82) [18]. Unfortunately, we saw a decrease in implementation over time; hence we were unable to show any effect after the second year [24]. Thorough examinations of the implementation process showed the importance of the degree of implementation for the intervention effects. Compared to students who were not exposed to the intervention, these analyses showed a stepwise increase in the effect of the intervention from OR 0.65 (CI: 0.43–0.97) for uptake of smoking for students exposed to medium implementation to OR 0.44 (CI: 0.32–0.68) for students exposed to full implementation of the intervention after the first year. Low implementation of the intervention did not significantly influence the smoking uptake among adolescents [20]. Further, subgroup analyses showed the importance of sufficient implementation of each of the three main intervention components [25].

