### Evaluation

#### Design

The X:IT II intervention will be evaluated by means of effect in a difference-in-difference design. Hence, all participating schools will receive the same intervention, and students from high and low social classes will be compared in the difference-in-difference design [32]. Process evaluation will be conducted at specific time points during the intervention period. Data collections are shown in Table 2.

**Table 2 Tab2:** Data collection of the X:IT II study – timeline, instrument and source of data

	Baseline September 2018	Intervention	Follow-up 1 May 2018	Intervention	Follow-up 2 April 2019	Intervention	Follow-up 3 April 2020
Students	Questionnaires (students start year 7)		Questionnaires (students end year 7)	Observations and interviews	Questionnaires (students end year 8)		Questionnaires (students end year 9)
School coordinators	Questionnaires		Questionnaires		Questionnaires		Questionnaires
Teachers		Monthly questionnaires on curricular activities (September – June)		Observations and interviews Monthly questionnaires on curricular activities (September – June)		Monthly questionnaires on curricular activities (September – June)	

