### Process evaluation

As was the case for the evaluation of X:IT [19–21, 25], we will conduct a detailed process evaluation among teachers and students focusing especially on those from low SEP. The process evaluation is based on questions added to the student and school coordinator questionnaires concerning the implementation of the study, e.g. the fidelity and dose of the intervention. Further, we will conduct ethnographic fieldwork at schools and qualitative interviews with students, school coordinators and other teachers involved in X:IT II. Information about the actual curricular activities is collected through monthly electronic questionnaires to teachers.

As the quality of implementation has a great impact on the conceivable effects, the process evaluation will have a specific focus on implementation. The organizational capacity for implementation at each school will be assessed through the baseline questionnaires for school coordinators. These measures are based on theories by Domitrovich et al. (2008) [34] and Saccia et al. (2015) [35], hence we will measure Motivation (i.e. the perceived relative advantage of X:IT compared to other programs, the complexity of X:IT and the priority for the school), General organizational capabilities (i.e. school culture, climate and leadership), and Innovation-specific capabilities (i.e. knowledge, skills and abilities needed for the intervention and the presence of a program champion). Further, the actual obtained implementation will be assessed at all follow-ups by both school coordinators and students, based on implementation measures developed in the evaluation of X:IT [20].

The qualitative data will focus on the school coordinator and teacher’s implementation of the X:IT II intervention. Thus, we will explore: 1) the teacher’s appraisal and reaction to the intervention and activities, 2) how the teachers experience and understand the problem that the intervention seeks to address, and 3) how the intervention activities are implemented in practice [36–38]. To understand adolescent’s smoking related behavior, we will investigate the influence of adolescent’s social relations and smoking in the daily environment [39, 40]. This will help us understand how the students perceive and receive the intervention.

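### The implementation analysis is modelled on the first X:IT trial, but X:IT II has no unexposed students, so it can show associations among exposed students and not effectiveness

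*Protocol article*

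**What the plan says.** The Discussion places an implementation analysis inside the effect evaluation: "Like in the X:IT study [20, 25], we will conduct analyses taking the actual implementation into account in the effect evaluation". The next sentence states the inference: "Hereby, we will be able to draw conclusions about the effectiveness of the X:IT evaluation". The analysis is to run at both school and individual level. The paragraph then notes that X:IT II has nearly as many intervention students as the first evaluation had, and concludes from this that the analyses are comparable.

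The section on the X:IT trial reports the earlier result: "Compared to students who were not exposed to the intervention, these analyses showed a stepwise increase in the effect of the intervention". The graded figures begin at the middle level, "from OR 0.65 (CI: 0.43–0.97) for uptake of smoking for students exposed to medium implementation". At the highest level the article gives "OR 0.44 (CI: 0.32–0.68) for students exposed to full implementation of the intervention after the first year". The Background describes that trial as "testing the implementation in 53 Danish schools compared to 41 control schools from 2010 to 2013".

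For X:IT II, the Design section says that "all participating schools will receive the same intervention". The recruitment section confirms that every interested school was taken in as an intervention school.

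On school differences, the Process evaluation section says: "The organizational capacity for implementation at each school will be assessed through the baseline questionnaires for school coordinators". The measures cover motivation, general capabilities such as culture, climate and leadership, and capabilities specific to the programme. No role for them in the implementation-effect analysis is stated.

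**The concern.** The earlier analysis could speak about effectiveness because it had an unexposed reference group. The new study does not have one, and a similar number of intervention students does not supply it.

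This matters because of what the main analysis cannot do. The difference-in-difference estimate contrasts SEP groups that are both exposed. It is zero if the programme works equally well in both, and also zero if it works in neither. The Hypotheses section nevertheless includes an overall 25% reduction in uptake. The implementation analysis is therefore the place where a reader would look for evidence of effectiveness, and the Discussion invites that use. Schools with better leadership, climate and motivation may implement more and also have less smoking for other reasons. Such a difference could then be reported as an effect of X:IT II.

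**Working it through.** The article gives no figure for this analysis, so there is none to reproduce. The check sets the two designs side by side and then illustrates what follows.

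**1. Reference group**

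| | First X:IT trial | X:IT II |
|---|---|---|
| Schools | 53 intervention, 41 control | 46 at baseline, all intervention |
| Unexposed students | yes | none |
| Reference for the graded odds ratios | unexposed students | not stated; can only be exposed students |

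The high-SEP comparison group of the difference-in-difference does not fill the gap, because those students receive the intervention too.

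**2. What remains estimable**

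An odds ratio against unexposed students is odds(level) / odds(unexposed), and X:IT II has no data for the denominator. Only ratios between levels remain. Taking the two first-trial odds ratios as coming from one model with a common reference (assumption), full versus medium is 0.44 / 0.65 = 0.68. That is a different quantity from 0.44.

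**3. How far the reference alone moves the result**

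Let L be the first trial's odds ratio for low implementation against unexposed. The article says only that low implementation had no significant influence, so L is unknown and could lie on either side of 1. Against low implementation, the odds ratio is OR / L. The range below is an assumption, symmetric on the log scale (1 / 0.7 = 1.43).

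| L (assumed) | Full: 0.44 / L | Medium: 0.65 / L |
|---|---|---|
| 0.7 | 0.63 | 0.93 |
| 1.0 | 0.44 | 0.65 |
| 1.43 | 0.31 | 0.45 |

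The same data can look weaker or stronger, and the direction cannot be known from the article.

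**4. Confounding with no programme effect (illustration)**

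Assume that half the schools have high capacity, with smoking at 13.4% in these and 17.9% in the others. These rates are borrowed from the power section purely as a plausible spread. Assume also that 70% of high-capacity and 30% of low-capacity schools implement well.

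- Smoking in well-implementing schools: 0.7 × 0.134 + 0.3 × 0.179 = 0.1475
- Smoking in the other schools: 0.3 × 0.134 + 0.7 × 0.179 = 0.1655
- Spurious odds ratio: (0.1475 / 0.8525) / (0.1655 / 0.8345) = 0.87

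Varying the split from 60/40 to 80/20 gives 0.93 to 0.81. With smoking at 12% and 20% by capacity, the range is 0.89 to 0.70.

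**5. Precision with 46 schools**

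With 50 students per school and an intraclass correlation of 0.053, the design effect is 1 + 49 × 0.053 = 3.597. Assume an even split, 23 against 23 schools. The effective size per group is 23 × 50 / 3.597 = about 320. At two-sided 0.05 (assumed, as the article states no level), power for 17.9% against 13.4% is about 35%. The rate detectable with 80% power is about 10.2%, an odds ratio of about 0.52. The contrast is imprecise even before adjustment.

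**The case against.** The best defence is that the Discussion says, just before the sentence at issue, that the quantitative process evaluation is based on recipients of the intervention, as in the earlier evaluation. Comparability may then mean only recipient analyses in both studies. That reading is possible for the comparability sentence, which should say so if it is meant. It does not rescue the effectiveness claim, which follows directly from placing implementation in the effect evaluation.

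Four stronger readings are tempting, and the document does not support them:

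- **A reader might infer that capacity is measured but left unused.** It serves the process evaluation. The Effect evaluation section names covariates only as examples, and the Statistical methods section provides for confounder adjustment without a list. A condensed article may leave that list to a fuller document. One can say only that no role in this analysis is stated.
- **A reader might infer that low implementation is the only possible reference.** The article names none. A graded score, single components, or implementation as a modifier of the SEP contrast are also open.
- **A reader might infer that both cited earlier analyses, references 20 and 25, used unexposed students.** The article documents this for the graded odds ratios (reference 20). For the component analyses (reference 25) it gives no reference group.
- **A reader might infer that the sponsor will set new odds ratios beside 0.65 and 0.44, with a known loss.** No such comparison is announced, and step 3 shows that the shift could go either way.

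It is also fair that this is a supporting analysis, and that the article already acknowledges the lack of randomisation as a limitation.

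**Conclusion.** The point holds as a mismatch between design and claim. The first trial's contrast with unexposed students cannot be estimated in X:IT II, and similar student numbers do not make the analyses comparable. Any implementation contrast is observational, among exposed schools or students. That conclusion rests on the text alone.

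The size of the resulting bias cannot be derived from the article. The spurious odds ratios of 0.93 to 0.70 show only what moderate confounding could produce under the assumed capacity split and smoking rates. The re-referenced odds ratios rest on an assumed value for low implementation.

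The planned SEP difference-in-difference is not affected. What is affected is the inference that the Discussion draws from the implementation analysis, and it should be corrected before results are reported.

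**What to change.** Revise the implementation paragraph of the Discussion as follows:

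1. State the reference category among exposed schools or students, or the graded implementation score to be used, for the school-level and the individual-level analysis.
2. Delete the comparability claim, or limit it to analyses among intervention recipients with the same reference in both studies.
3. Report the result as an association among exposed students, not as effectiveness of X:IT II.
4. Include baseline organisational capacity and motivation, baseline smoking and SEP as adjustment variables in this analysis. All are already collected.

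A within-school analysis across the follow-ups is an optional sensitivity analysis only. It would need wave or grade effects: implementation fell over time in the first trial and smoking rises from very few users at the start of grade 7, so without them age alone would create an association.

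The changes need no new data. The price is a more modest claim and somewhat wider intervals with 46 schools.

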## Abbreviations

RCT: randomized controlled trial
SEP: socioeconomic position
